# An app-based physical activity intervention for people with hip and knee osteoarthritis: protocol for the PIANISSIMO feasibility study

**DOI:** 10.1186/s40814-025-01744-z

**Published:** 2025-12-05

**Keywords:** Osteoarthritis, Hip, Knee, mHealth, Physical activity, Health promotion, Healthy lifestyle

## Abstract

**Background:**

Osteoarthritis is one of the most prevalent musculoskeletal disorders. In osteoarthritis patients, physical activity has been shown to be an effective tool to improve quality of life as well as to reduce the pain associated with the disease and the development of additional comorbidities. Yet osteoarthritis patients often do not meet the level of physical activity recommended to stay in good health. The PIANISSIMO study primarily aims to test the adherence of people with hip and knee osteoarthritis to a 6-month intervention for the promotion of physical activity specific to this population using a dedicated mobile app.

**Methods:**

The PIANISSIMO study is a longitudinal, interventional feasibility study conducted through a dedicated mobile app. A total of 151 participants with hip or knee osteoarthritis will be included. The app will collect data and deliver the intervention. Data will be collected through questionnaires (i.e. demographic data, osteoarthritis history, sport history, pain and functional capacities, app evaluation) and from Apple Health/Google Fit apps. The PIANISSIMO study will use a 6-month physical activity intervention based on the *Capability**, **Opportunity**, **Motivation–Behaviour* change theory. Participants will receive a text notification on a daily basis; they will be asked to set their daily steps goal for the next week, and the mobile app will deliver feedback on daily step count and whether the goal of the week has been reached. The primary outcome of this study is the adherence (i.e. connection log and rate of answered questionnaires) to the app-based physical activity intervention. Retention will be calculated as the number of drop-outs over 6 months of follow-up. Moreover, the acceptability of the app and intervention by the study participants will be evaluated through a questionnaire.

**Discussion:**

This mobile app was designed to provide a digital solution for the promotion of physical activity in people with osteoarthritis. If the feasibility of delivering a physical activity intervention through the mobile app is confirmed, the efficiency of the tool in improving the quality of life of people with hip and knee osteoarthritis should then be properly investigated.

**Trial registration:**

Registration number

NCT06385028 (https://clinicaltrials.gov/study/NCT06385028)

Protocol version 1.2

**Supplementary Information:**

The online version contains supplementary material available at 10.1186/s40814-025-01744-z.

## Introduction

Osteoarthritis (OA) is the second most prevalent musculoskeletal disorder [1]. In 2019, it was reported that this degenerative condition mostly affected the hip and knee, with approximately 400 million prevalent cases in the world [2]. In 2017, Western Europe had an age-standardised prevalence rate of hip and knee osteoarthritis of 38.6 per 1000 inhabitants and an incidence rate of 2.01 per 100,000 person-years—reflecting increases of 7.2% and 8.0%, respectively, since 1990 [3]. A recent meta-analysis of 63 studies, involving 5397 knees, showed a prevalence of MRI-detected OA features ranging from 19 to 43% in adults over the age of 40 [4]. A study led in Germany found that the prevalence of people over 60 years old presenting with hip or knee OA was almost 22% [5]. This trend can be explained by the population ageing as well as an increased prevalence of obesity and traumatic injuries at an early stage of life, which will even further increase the OA burden in the next years [6–8].

The economic burden associated with OA is high for both patients and society, particularly due to work loss, premature retirement, disability and high health care costs [9]. Moreover, a recent meta-analysis has shown that hip and knee OA increase the risk of developing atherosclerosis and cardiovascular diseases [10]. Another meta-analysis showed that OA patients have higher risks of myocardial infarction or stroke compared with control subjects [11], likely due to a lack of physical activity [12].

In addition to being cardioprotective in the general population [13], the practice of physical activity has been shown to reduce symptoms of OA such as fatigue [14], depression [15] and pain [16], as well as increase quality of life [17]. In line with these benefits, the European Alliance of Associations for Rheumatology (EULAR) recommends physical activity, weight management and occasional painkillers as the first-line treatments for hip and knee OA [18]. The general physical activity recommendations, including cardiorespiratory fitness, muscle strength, flexibility and neuromotor performance, are considered to be feasible and safe for OA patients [3].

Pain is the most disabling symptom of OA, being the major driver of healthcare seeking and clinical decision-making [19]. Expensive and reactive treatments (i.e. analgesic drugs, joint replacement surgeries) are often favoured to overcome OA symptoms, and effective lifestyle behaviour strategies such as physical activity or weight loss are currently underused [20, 21]. Patients with OA actually often still believe that physical activity will further damage their joints; thus, they doubt the effectiveness of physical activity and have fatalistic beliefs about OA-related pain [22]. As a result, most patients with OA do not meet the levels of physical activity recommended to expect optimal health outcomes [23]. As low physical activity is associated with low physical capacities [24, 25], patients with OA often fall into this vicious circle where the lack of physical activity and capacities leads to the development of comorbidities [12].

The most recent EULAR guidelines for the care of OA recommend including behaviour change techniques in order to help patients go beyond the fear of pain and increase the long-term adhesion to an active lifestyle [18]. These behaviour change techniques have been identified by Michie et al. [26] as tools to implement the *Capability, Opportunity, Motivation–Behaviour* (COM-B) framework [27]. The COM-B framework states that behaviour change requires individuals to feel empowered with *capability* (i.e. physical and psychological abilities to perform the behaviour) and have the *opportunities* (i.e. social and psychological factors that enable the behaviour) in order to increase *motivation* (i.e. internal process that triggers the behaviour) [27]. Based on this framework and evidence from mobile health (mHealth) interventions, we identified that the most important behaviour change techniques for our target population are goal setting [28], educational content [29] and feedback on performance [30]. The challenge of a non-pharmacological therapy to promote a change of behaviour to a healthier and more active lifestyle is to overcome physical, psychological and social barriers. To achieve this goal, several recommendations have been made. First, knowledge about the practice of physical activity in patients with OA should be widely disseminated [20, 31]. Then, the effectiveness of these educational programmes’ dissemination should be improved by suggesting a wide range of options and opportunities to practice physical activity, in line with the WHO health campaign “Every move counts towards better health” [32]. Lastly, patients should be able to monitor their physical behaviour [20, 31]. Thus, self-monitoring and individual goal setting enable participants to tailor their daily steps goal to their current levels of fatigue and pain.

For most chronic conditions, physical activity interventions have been delivered by rehabilitation centres. However, for most patients, frequent trips are time-consuming and tedious [33, 34]. These logistical barriers could explain the low adherence to physical activity post-intervention [35], reducing the long-term benefits on health. In healthy participants, mHealth interventions have shown to be effective in increasing physical activity [36] and reducing sedentary behaviour [37]. A recent meta-analysis showed that feedback and monitoring, as well as goal planning, are efficient ways to promote a change in behaviour using mHealth interventions [38]. A preliminary study suggests that a 9-week web-delivered physical activity intervention is plausible, feasible and acceptable for patients with hip and knee OA [39]. The “bring your own device” assessments allow the use of participants’ own devices to record real-life data [40, 41]. The use of these digital interventions would allow increasing post-intervention adherence by implementing the behaviour (here physical activity) in the everyday life of the study participants during the intervention. Thus, this feasibility study will be conducted before implementing a large-scale trial aimed at increasing the physical activity behaviour of people with hip and/or knee osteoarthritis using an app. It will assess participant engagement toward the intervention by evaluating adherence, retention and acceptability to a 6-month intervention.

### Objectives

The PIANISSIMO feasibility study primarily aims to test the adherence of participants with hip and knee OA to a 6-month intervention for the promotion of physical activity using a dedicated mobile app.

The secondary aims are to assess the retention and acceptability of participants with hip and knee OA to the intervention.

Moreover, the study aims to investigate the daily steps pattern in participants with hip and knee OA during the 6-month intervention and to explore the relationship between physical activity and pain. Finally, physical activity patterns of people with hip and knee OA over the 6-month period following the end of the intervention will be analysed.

## Methods

### Study design

The PIANISSIMO study is a longitudinal, one-arm interventional, feasibility study funded by the *Oeuvre Nationale de Secours Grande-Duchesse Charlotte*. This protocol has been designed according to previously established guidelines [42]. The protocol has been written according to the adjusted version of the SPIRIT 2013 statement: Defining standard protocol items for clinical trials [43], including indication of Thabane and Lancaster [44], clarifying items of the CONSORT 2010 statement [45] regarding feasibility studies.

The entire study will be conducted through a dedicated mobile app specifically designed for the purpose of the study. The mobile app will collect data and deliver the intervention. Data will be collected through questionnaires (i.e. demographic data, OA history, sport history, pain and functional capacities, app evaluation) and from Apple Health/Google Fit apps. Adverse event (AE) can be reported at any time in the app. The intervention will not interfere with participants’ medical treatments, which will remain the decision of the participant in agreement with his physician. There is no financial compensation for trial participation.

### Study population

All participants must meet the following criteria to be eligible: Male or female aged ≥ 18 years old; diagnosed with any stage of hip or knee OA; live or work in Luxembourg; download and engage with the mobile app by fulfilling questionnaires; understand one of the following languages: English, French or German; and have a smartphone with internet connection. Presenting rheumatoid arthritis is the only exclusion criteria.

### Sample size

Assuming a minimum adherence rate of 67% in the last month, a 95% confidence level and an acceptable margin of error of 7.5%, a minimum of 151 participants with hip or knee OA is required.

### Recruitment

Advertisement for the PIANISSIMO study will be done in social media and by display of flyers in hospital and general practitioner offices. In both cases, a short explanation of the study will be followed by a QR code that will redirect participants to the App Store and Google Play Store to download the app. Then, the participants will access the detailed study protocol, participant’s rights for human clinical research and a data protection notice. The participants willing and able to agree to the terms of the study enrolment, as well as fulfilling eligibility criteria, will be included after the written informed consent form is electronically signed. A copy of these documents will be available for participants to consult in the mobile app during the study.

### Intervention

The PIANISSIMO study will use a 6-month physical activity intervention, based on the COM-B behaviour change theory [27], and including behaviour change techniques (BCT) extensively described in the literature [26]. The BCT used in the present study is detailed in Table 1.

**Table 1 Tab1:** Behaviour change techniques used and mobile app-based intervention delivery

Behaviour change technique	Intervention
1. Provide information/instructions on the following:	Daily text notification
Consequences of behaviour *in general*	“Physical activity plays a role in hypertension control” “Physical activity helps to prevent falls and fall-related injuries”
Consequences of behaviour *to the individual*	“Physical activity WILL NOT damage your joints” “Physical activity can reduce depression in osteoarthritis patients”
Where and when to perform the behaviour	“Stand up and walk during TV commercials—go for a tea, a glass of water”; “Stretch for 5 min when you wake-up”
How to perform the behaviour	“Did you know gardening is physical activity?” “Stay hydrated! The effort will be less strenuous”
Time management	“If you plan it, you will do it. Schedule even short walks!” “At home or at work, set an alarm every 30 min to remind yourself to stand up. No need to go far!”
2. Fear arousal	Daily text notification “Inactivity is the 4th cause of premature death (before 70 years) and global mortality” “Low physical activity is associated with a worsening of pain and physical function”
3. Goal setting	Weekly goal setting in order to increase physical activity until the end of the 6-month intervention
4. Feedback on performance	Graphical representation of daily steps matched against the goal setting

The behaviour change techniques used in PIANISSIMO are based on [26]

First, participants will receive a text notification on a daily basis (except on Sunday). During the first week, notifications will mainly focus on how to practice physical activity, i.e. pointing out the participants’ capabilities and the opportunities to practice. The content of the notifications will then progressively address further their motivation, including knowledge about the health benefits of physical activity (a complete list of notifications is available in Additional file 1
).

Second, participants will be asked to set their daily steps goal as their PA target for the next week every Sunday by a text notification. In case no response is given, another reminder will be set for the next day at 8 am. It is expected that participants will set a gradual daily steps goal, empowered by the knowledge they received and their increased PA capacities. Daily steps will be retrieved by an Application Programming Interface (API) in the Apple Health/Google Fit applications. The API centralises the data from the participants’ phone or from a connected watch, if a wearable device is connected to the phone. Thus, the PIANISSMO app will allow participants to follow their daily steps on a graph matched against their week’s goal.

Third, the mobile app will deliver feedback on daily step count and whether the goal of the week has been reached.

### Data collection

Figure 1 provides a detailed graphical representation of the data collection in the PIANISSIMO study.

**Fig. 1 Fig1:**
[figure not shown]
Study scheme of the PIANISSIMO study. SF-WOMAC, Short Form Western Ontario McMaster University Osteoarthritis Index

### Data at inclusion

Participants’ demographics will be obtained at inclusion. This will include information on sex, age, height, weight, tobacco exposure (smoker, ex-smoker, never smoked), alcohol intake (doses per week), employment status (employed, unemployed, retired, not working, student), job category (list of minor groups of the International Standard Classification of Occupations [ISCO] classification), level of education (no formal education, primary education, lower secondary education, upper secondary education, post-secondary non-tertiary education, short cycle tertiary education, bachelor’s or equivalent, master’s or equivalent, doctoral or equivalent), annual income, country of residence, type of residence (apartment, house) and comorbidities (heart disease; hypertension; pulmonary disease; diabetes; ulcers or stomach disease; kidney disease; anaemia or blood disease; cancer; depression; OA, degenerative arthritis; back pain; rheumatoid arthritis—list from the self-administered comorbidity questionnaire [46]). OA will be characterised according to the affected joints (left/right knee, left/right hip, left/right foot, left/right elbow, left/right shoulder, left/right hand, spine), pain management treatment (analgesic levels 1, 2 or 3; physiotherapy), duration since diagnosis, mean of diagnosis (consultation only, consultation and imaging, imaging only), previous treatments (surgery, injections, thermal cure, physical activity) and symptomatic severity (assessed with a short form of the Western Ontario McMaster University Osteoarthritis Index [SF-WOMAC] [47, 48] described in detail below). Information on sports practice history will be collected including sport disciplines, frequency and duration of practice of previous and ongoing practice (Fig. 1).

### Follow-up data

Throughout the study, participants will be asked to complete a brief pain evaluation questionnaire that will be sent randomly once a week via the mobile app. In these questionnaires, participants will first be asked whether they have experienced any joint pain since the last time they completed the questionnaire. If they report pain, they will be asked to provide the following details: location of the pain (left/right knee, left/right hip, left/right foot, left/right elbow, left/right shoulder, left/right hand, spine), the intensity of the pain (rated on a Likert scale ranging from 0 [no pain at all] to 10 [worst pain ever]), any additional treatment used (analgesic levels 1, 2 or 3, cold application, alternative medicine), timing of the pain (wake up, morning, afternoon, evening, night), context of the pain (resting, walking exclusively, using the joint, carrying heavy loads) and the weather condition (rain, snow, cloudy, sunny) and perceived conditions (hot, mild, cold). They will also have the possibility to report a pain crisis at any time using the same questionnaire.

Participants will also be asked to answer the SF-WOMAC questionnaire [47, 48] monthly. This version comprises two parts, addressing pain and function, respectively. The first part comprises three specific questions addressing the average severity of the pain in the last 48 h while walking, stair climbing and resting. The second part addresses the average level of difficulty performing the functions during the last 48 h of descending stairs, ascending stairs, rising up from sitting, walking on flat, getting in/out of a car, going shopping, putting on socks and getting on/off the toilets. The participant will be asked to answer all 11 questions using a Likert scale ranging from 0 (none), 1 (slight), 2 (moderate), 3 (severe), to 4 (extreme).

At the end of the intervention, participants will be invited to give their feedback about the mobile app through a qualitative standardised questionnaire. Participants will be asked if the mobile app helped them increase their physical activity level, if they think they could maintain the actual level of physical activity without the intervention, what motivated them the most (goal setting, text notifications, both, nothing), if they liked the app and why, if they found that the app was adapted to their health condition, if they would recommend the app and how they heard about it. A free comment section will also be available. After 2 weeks without any interaction (i.e. no response to the questionnaire or connexion to the mobile app), the participant will be considered a drop out.

During the subsequent 6-month follow-up period, the pain evaluation questionnaire will be sent randomly twice a month (Fig. 1).

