### Outcomes

#### Primary outcome

The primary outcome of this study is adherence to the mobile app-based physical activity intervention, measured using three indicators: the number of logins per week, the percentage of weekly goals set and the percentage of questionnaires completed by the participant during the 6 months. Adherence will be considered good if the number of logins per week does not decrease by more than 33% between the first and the last month and if at least 50% of the weekly goals are set and questionnaires are completed over the intervention.

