### Statistical analysis

Data management and analysis will be performed using R software (version 2023.6.1.524). Descriptive statistics will be computed to describe baseline participants’ sociodemographic, feasibility and acceptability data. Frequencies and percentages will be reported for categorical variables and means and standard deviations for continuous variables. The evolution of daily step count over time, as well as the bidirectional relationship between daily step count and pain, will be explored using linear mixed-effects models. Open-ended question responses will be analysed using a qualitative content analysis inductive approach as described by Elo [49].

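### The pain form looks back to its last completion, so the recall window varies with compliance and study phase, which can distort the exploratory activity-pain analysis

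*Protocol article*

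**What the plan says.** Under Follow-up data, the protocol article describes "a brief pain evaluation questionnaire that will be sent randomly once a week via the mobile app". Its opening item asks "whether they have experienced any joint pain since the last time they completed the questionnaire"; location, 0-10 intensity, treatment, timing and context follow only if pain is reported. The same section adds: "They will also have the possibility to report a pain crisis at any time using the same questionnaire". After the intervention the frequency falls: "During the subsequent 6-month follow-up period, the pain evaluation questionnaire will be sent randomly twice a month".

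Three other places bear on this:

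- Primary outcome counts adherence as good if, among other conditions, "at least 50% of the weekly goals are set and questionnaires are completed over the intervention".
- The dropout rule under Follow-up data applies "After 2 weeks without any interaction (i.e. no response to the questionnaire or connexion to the mobile app").
- Statistical analysis says that the "bidirectional relationship between daily step count and pain, will be explored using linear mixed-effects models". Exploratory outcomes gives cumulated weekly steps as one example of the activity measure.

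The article gives no fixed look-back for the pain form. The monthly SF-WOMAC, in the same section, uses a fixed 48-hour recall.

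**The concern.** The look-back of the pain item is set by each participant's own completion history. A longer look-back gives more opportunity for at least one painful episode, so a yes becomes more likely even if the joint is no worse. Window length varies for three reasons: the random prompt day, missed forms, and the lower sending frequency in follow-up. The second reflects engagement with the app, which may itself be related to activity. A 7-day step total would then be paired with a pain report covering anything from one day to several weeks, and part of any step-pain association could come from window length alone.

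Crisis reports are a separate difficulty. They are filed because of pain, so they add pain-selected records to the series. As the item is worded, they may also shorten the window of the next scheduled form.

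**Working it through.** **The plan's own figure.** The only computed design figure is the sample size: 1.96² × 0.67 × 0.33 / 0.075² = 150.99, rounded up to 151. It reproduces and does not depend on this point. The plan gives no figure for the pain window.

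**Inputs from the article.** One random prompt per week in the intervention; two random prompts per month in follow-up; 50% completion accepted as good. **Assumptions, not in the article:** the prompt day is uniform within the week; pain is independent from week to week; true weekly probability q of any joint pain is 0.30, 0.50 or 0.70.

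**Step 1, window length.**

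- Weekly phase, full compliance: gap = 7 + (next day − previous day), each day 0 to 6. Range 1 to 13 days, mean 7, SD 2.8.
- Weekly phase, 50% completion: mean 7 / 0.5 = 14 days. If forms are missed at random, the SD is about 10 days and the 5th to 95th percentiles are 3 to 34 days.
- Follow-up, full compliance: mean 365.25 / 24 = 15.2 days, 2.17 times the weekly phase.
- The dropout rule does not cap these windows. Read as requiring neither a response nor a connection, it is not triggered by someone who opens the app but skips the form.

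**Step 2, probability of a yes with no true change.** For a window of d days, P = 1 − (1 − q)^(d/7).

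For random 50% completion the window is K weeks, with K geometric, so P = 1 − 0.5(1 − q) / [1 − 0.5(1 − q)]. For q = 0.30 this is 1 − 0.35/0.65 = 0.46.

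| Window | q = 0.30 | q = 0.50 | q = 0.70 |
|---|---|---|---|
| exactly 7 days | 30% | 50% | 70% |
| random 50% completion, weekly phase | 46% | 67% | 82% |
| exactly every second form (14 days) | 51% | 75% | 91% |
| exactly 15 days | 53% | 77% | 92% |

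The 14-day and 15-day rows put a single window length into a concave formula, so a spread of windows around the same mean gives less. Averaging the formula over the random gaps at full compliance gives 29/48/66% in the weekly phase. If follow-up prompts fall on two random days in every 30, it gives 48/67/80% there. The contrast remains, somewhat smaller.

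**Step 3, sensitivity to how frequent pain is.** With a constant daily probability, again assumed independent, P = 1 − (1 − daily probability)^d:

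| Daily probability | 7 days | 15.2 days |
|---|---|---|
| 0.01 | 6.8% | 14.2% |
| 0.05 | 30.2% | 54.2% |
| 0.10 | 52.2% | 79.9% |
| 0.30 | 91.8% | 99.6% |

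The shift is large for intermittent pain and small once most weeks already contain pain. Pain that persists from week to week also shrinks it, because extra days then add little new information.

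**Step 4, intensity.** The article does not say whether the 0-10 rating is of worst or average pain. A worst-pain rating would rise with the window; an average need not. No size can be given.

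**Step 5, after the fix.** With a fixed 7-day recall, d = 7 at every administration, so P = q in both phases and at every level of completion.

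**The case against.** The strongest reply is that little depends on this. The article's primary aim is adherence and its secondary aims are retention and acceptability; the activity-pain relation is exploratory. That stands, and it limits the severity.

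The data also allow repair. Steps are recorded daily and the database keeps collection dates, so steps can be summed over the actual window and its length modelled. That stands too, although a covariate cannot recover when within a long window the pain occurred. The model statement does not name its pain variable, and the SF-WOMAC has a fixed recall. But the SF-WOMAC is monthly and cannot replace the weekly form.

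The present wording has a merit: consecutive windows are contiguous and do not overlap. A fixed recall gives that up.

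A reader might go further than the article supports in four ways:

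- *The model cannot separate the two directions.* This presumes that pain and steps are analysed over the same days. The article does not say so, and lags and centring are ordinary analysis-plan content.
- *Follow-up will show a false rise in pain.* No comparison of pain between phases is stated. For months 6 to 12 the article plans activity patterns and maintenance of behaviour. The longer window matters there only if pain from both phases is pooled or compared.
- *Less engaged users will in general show more pain.* This holds for the yes/no item when pain is intermittent, not for persistent pain and not necessarily for intensity.
- *Crisis reports reset the window.* The article says only that the same form is used, not how the app words the next prompt.

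The article also first describes weekly sending as applying to the whole study. The follow-up figure relies on the later, more specific sentence.

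**Conclusion.** The point holds in limited form. As worded, the look-back runs from one day to several weeks and depends on completion and phase, and nothing else in the article corrects this. For the yes/no item, a true weekly probability of 30/50/70% would be reported as about 46/67/82% under random 50% completion and about 53/77/92% over a 15-day window. Both rest on independent weeks and on assumed pain probabilities.

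The exposure is confined to the exploratory activity-pain analysis. The feasibility criteria use no pain scores: completing a pain form counts towards adherence, but its content does not. Severity is minor to moderate; it is worth correcting because the source is a single item's wording.

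**What to change.** - Reword the opening item to a fixed recall of the last 7 days, in both phases.
- Flag crisis reports, and analyse them as separate events, apart from the scheduled forms.
- In the activity-pain models, sum steps over the same 7 days that the pain item covers.
- For data already collected, sum steps over the actual window and include days since last completion as a covariate. This is a partial remedy.

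**Cost.** One app question is reworded and a few lines are added to the analysis text. Coverage also becomes uneven. In the weekly phase with random prompts and full compliance, the mean shortfall per gap is half the mean absolute difference between two uniform days: (48/21)/2 = 1.14 days. So 1.14/7, about 16% of days, fall outside any window, and by symmetry the overlap is equally large. In follow-up a 7-day recall covers at most 7/15.2 = 46% of days, so at least about half go unrecorded unless reported as a crisis.

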### Secondary outcomes

Retention will be calculated as the number of dropouts over time during the 6 months. A retention of ≥ 33% of participants at the end of the 6 months will be considered a successful outcome. Moreover, the acceptability of the mobile app and the intervention by the study participants will be assessed qualitatively through a combination of open- and closed-ended questions. This will cover usefulness, most motivating features, user-friendliness, adaptability to condition, intent to continue physical activity and suggestions for improvement. Acceptability will be considered good if ≥ 70% of responses regarding usefulness, user-friendliness and adaptability to condition are positive. Feasibility will be validated if adherence, retention and acceptability meet the positive outcomes specified above.

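### The closed question on what motivated participants most has no option for feedback on performance, one of the three intervention components

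*Protocol article*

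**What the plan says.** The Introduction to the protocol article gives the rationale for the intervention and states that "the most important behaviour change techniques for our target population are goal setting [28], educational content [29] and feedback on performance [30".

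The Intervention section then describes delivery in three numbered parts:

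- "First, participants will receive a text notification on a daily basis (except on Sunday"
- "Second, participants will be asked to set their daily steps goal as their PA target for the next week every Sunday by a text notification"
- "Third, the mobile app will deliver feedback on daily step count and whether the goal of the week has been reached"

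Table 1 in the same section gives feedback on performance its own row, separate from goal setting, with this description of delivery: "Graphical representation of daily steps matched against the goal setting".

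Under Follow-up data, the end-of-intervention questionnaire asks "what motivated them the most (goal setting, text notifications, both, nothing". Under Secondary outcomes, the acceptability assessment is said to include this topic: "This will cover usefulness, most motivating features, user-friendliness, adaptability to condition".

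**The concern.** The answer list matches a two-component intervention, but the protocol delivers three. A participant for whom the step graph or the goal-reached message was the main motivator has no answer that says so. The word *both* confirms that the list was built around two features, and *nothing* closes it at the other end. No *other* option is shown.

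What is at stake is the descriptive result for one acceptability domain. If the shares are tabulated as they stand, a reader of the results may take them as the relative appeal of the app's components. They would be that only for two components out of three, with answers from people motivated by the third mixed in.

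**Working it through.** The protocol gives no figure for this item, so there is nothing to reproduce. The check compares the component list with the answer list.

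**Step 1: components against options**

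| Component | Introduction | Table 1 | Intervention text | Can be chosen alone | Can be chosen in combination |
|---|---|---|---|---|---|
| Text notifications (educational content) | named | own rows | First | yes | yes, through *both* |
| Goal setting | named | own row | Second | yes | yes, through *both* |
| Feedback on performance | named | own row | Third | no | no |

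**Step 2: answer patterns.** Suppose each component either is or is not among what motivated a person most, with ties allowed, as *both* implies.

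- Two components give 2² = 4 patterns: neither, the first, the second, both. These are exactly the four options listed, so the list is complete for two components.
- Three components give 2³ = 8 patterns. Feedback is present in 2² = 4 of them. None of those four can be recorded.

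**Step 3: effect on the reported shares.** Let f be the share of respondents whose true answer includes feedback. Let r_k be the fraction of them who pick option k, with the r_k summing to 1. If everyone else answers as they mean to, then

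reported share of option k = true share of option k + f × r_k.

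Two results follow:

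- Each reported share is at least as large as the share of people whose true answer is exactly that option.
- The reported gap between goal setting and notifications equals the true gap plus f × (r_goal − r_notification). That extra term can have either sign.

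The protocol gives neither f nor the r_k, so the size and direction of the distortion cannot be calculated. The only certain result is that this item cannot record a selection of feedback.

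**Step 4: reach of the item.** Secondary outcomes defines good acceptability as at least 70% positive responses on usefulness, ease of use and fit to the participant's condition. The motivation item is not among these. Adherence is defined from logins, goals set and questionnaires completed, and retention from dropouts. Neither uses the item. No criterion in the feasibility verdict depends on it.

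**The case against.** Four arguments can be made on the other side.

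1. **Feedback is not lost from the questionnaire.** Participants are also asked why they liked the app, there is space for free comments, and the Statistical analysis section plans an inductive content analysis of open answers. This stands. A reader might infer that feedback is bound to score zero in the acceptability results. That is true of the closed item only. Unprompted remarks, however, are not on the same scale as selected options and do not correct the tabulated shares.

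2. **Goal setting and feedback overlap.** The graph is first mentioned in the goal-setting paragraph, it shows steps against the weekly goal, and the third component reports whether that goal was met. Someone motivated by seeing progress could reasonably tick goal setting. This also stands in part. It means the protocol does not support saying that such a person must answer wrongly, or that *nothing* is materially inflated. But the Introduction, Table 1 and the third numbered part all treat feedback as separate, and merging it with goal setting is itself a loss of the information the item seeks.

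3. **The article paraphrases the form.** Ease of use, for example, is an acceptability topic under Secondary outcomes but is not among the items described under Follow-up data. The description is therefore not a full transcript. Even so, *both* and *nothing* make this particular list read as a complete answer set, not as examples.

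4. **No stated decision depends on it.** This stands. A reader might infer that the item will determine which components enter the later trial. The Discussion says only that the study's data will help plan further trials, and it gives no rule for selecting components. In a one-arm study a self-reported preference could not isolate component effects in any case.

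**Conclusion.** The point holds for the closed item. Its answer list does not match the protocol's own account of the intervention, and the shares it yields cannot be read as a ranking of the three components. This rests on two readings: that the four listed options are the complete set, which their wording supports, and that feedback is a component in its own right, as three places in the article state.

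The severity is minor. Only one descriptive result is affected. The acceptability criterion and the feasibility verdict stand as they are. It may be tempting to put a percentage on the misplaced answers, but the protocol offers no basis for one.

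**What to change.** Add an answer option such as *feedback on steps (graph / goal reached)*. Replace *both* with wording that covers combinations of three components. Alternatively, let participants tick every feature that motivated them and then mark the strongest, which also separates feedback from goal setting for those who valued each.

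The cost is one extra option and one reworded option in an in-app form. No threshold, sample size or outcome definition changes. The protocol article does not state how many participants, if any, have already reached the end of the intervention. Any answers given under the present options should be tabulated separately from those given under the revised list. If the form can no longer be changed, the results should state that feedback was not offered as an answer and should not present the shares as a comparison of all components.
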